## Abstract

**Background:**

This paper presents the pilot study and protocol for a randomised controlled trial to test the effectiveness of a psychological, family-based intervention to improve outcomes in those with poorly controlled type 2 diabetes. The intervention has been designed to change the illness perceptions of patients with poorly controlled type 2 diabetes, and their family members. It is a complex psychological intervention, developed from the Self-Regulatory Model of Illness Behaviour. The important influence the family context can have in psychological interventions and diabetes management is also recognised, by the inclusion of patients' family members.

**Discussion:**

This study is the first of its kind to incorporate the evidence from illness perceptions research into developing and applying an intervention for people with poorly controlled diabetes and their families. This study also acknowledges the important role of family members in effective diabetes care.

**Trial registration:**

ISRCTN62219234

## Background

### The importance of glycaemic control

A large body of evidence is now available showing that good glycaemic control in diabetes (as assessed by HbA1c) is associated with improved outcomes [1-6]. Current international guidelines recommend a HbA1c target level of approximately 6.0%–7.5% [7-9]. However, achieving good glycaemic control requires patients to follow a treatment regime which involves lifelong behavioural self-regulation through lifestyle changes (e.g. diet, exercise) and self-management skills (monitoring symptoms, testing blood glucose, taking medication). Many patients can have difficulties following this treatment regime[10,11] and evidence suggests only about one-third of patients with type 2 diabetes achieve glycaemic targets [12]. This has led to a call for concerted efforts to increase the proportion of patients achieving good glycaemic control [12]. It would seem prudent then, for interventions aiming to improve outcomes in diabetes, to be particularly aimed at patients having difficulties controlling their illness.

### Psychological interventions

There is growing awareness of the important role of psychosocial and behavioural factors in diabetes management [10], as highlighted by recommendations to integrate psychosocial support into routine diabetes care [8,13]. Psychological interventions to improve outcomes in diabetes have been systematically reviewed by a number of different authors, [14-16], with pooled trial results suggesting psychological interventions in diabetes reduce HbA1c by a clinically significant 1% [17]. Psychosocial interventions targeting those in poor control of their diabetes have been successful in improving glycaemic control in patients with type 1 diabetes [18-20], however there appear to be few interventions targeting those with poorly controlled type 2 diabetes.

### Illness perceptions

One psychological approach that has been widely used in diabetes research is based on the Self-Regulatory Model of Illness Behaviour [21,22]. This approach proposes that in response to an illness, or health threat, people form their own common sense beliefs or *illness perceptions *about their illness and treatment. (The terms 'illness perceptions', 'illness representations', 'illness cognitions', and 'illness beliefs' are often used interchangeably in the literature; here the term illness perceptions is used.) These illness perceptions influence the types of health-related behaviours and coping behaviours which a patient uses for managing their illness and which may impact on disease outcomes. Research into illness perceptions [23,24] suggests they encompass five broad dimensions: identity, timeline, causes, consequences, and curability/controllability (see Figure 1: the five domains of illness perceptions). Patients' perceptions of their diabetes have been found to influence self-management behaviours [25-30] which may, in turn, impact on glycaemic control [31,32].

**Figure 1 F1:**
[figure not shown]
The five domains of illness perceptions [21].

Patients in poor control of their diabetes have been found to have distinctly different perceptions of their illness than those in good control. A study of patients with type 2 diabetes [33] found that compared to patients in good control (HbA1c < 7), those in poor control (HbA1c > 8.5) had a stronger perception that their illness was caused by hereditary factors, reported suffering from more diabetes-related symptoms, perceived diabetes as having significantly greater impact on their lives, and reported more negative emotions in relation to their illness. Interventions focusing on changing these illness perceptions amongst patients in poor control may lead to improved illness outcomes, including better glycaemic control. A brief intervention (3 sessions)[34] designed to alter patients' perceptions about their recent MI was associated with significant positive changes in patients perceptions of their illness, as well as a significantly earlier return to work and lower rates of angina symptoms. However, there would appear to be few interventions which attempt to improve outcomes by explicitly targeting and measuring changes in illness perceptions in of type 2 diabetes.

### The role of the family

A comprehensive understanding of how people think about, and thus manage, their illness can only be reached by taking into account the social and family context in which the thoughts were developed [35]. The possible impact of the family context on illness perceptions is particularly relevant for diabetes, as most of the self-regulatory behaviours involved in the self-management of diabetes occur at home. Evidence from a small number of studies suggests that the illness perceptions of family members may influence disease outcomes. Differences between the illness perceptions of patients with chronic illness and their spouses have been found to have a strong impact on patients' adaptive outcomes [36], while similar positive patient and spouse perceptions about the identity and consequences of MI have been found to be associated with better physical, psychological, social and sexual functioning [37]. Substantial differences have been found between family members' and patients' perceptions of type 2 diabetes [38]. Family members perceived diabetes as a more serious illness, and as having a greater impact on daily life, than those with the illness. Those with diabetes were unaware of their family member's heighten concerns and had a more relaxed approach to living with diabetes. Interventions targeting the illness perceptions of patients and families would seem a promising area for future research in view of the evidence suggesting that the degree of congruence between patient and spouse illness perceptions is related to illness outcomes. A hypothesised model by which family members illness perceptions may influence patient health outcomes in diabetes is presented in figure 2. (Figure 2: how family members may influence outcomes in diabetes.)

**Figure 2 F2:**
[figure not shown]
How family members may influence outcomes in diabetes.

### Family interventions in type 2 diabetes

A number of authors have noted that the role of family factors in adult diabetes intervention research has been neglected, particularly in type 2 diabetes. [10,39-41] This is despite recent evidence suggesting that the inclusion of a family member in psychosocial interventions for chronic illness may improve illness outcomes [42-45] A recent systematic review [46 Zhang & Fisher, 2005 #516] identified only one published RCTs that included a patient's family member in an intervention for patients with type 2 diabetes [47]. This study [47] was based on a behavioural weight loss intervention, which included patients' spouses. The study found a significant weight loss in both control and family group. However, there was a significant interaction of treatment and gender, with women doing better than men when treated with their spouses as opposed to being treated alone.

This paper presents the pilot study and the protocol for a RCT that is currently underway to test the effectiveness of a family-based intervention, designed to change the illness perceptions of patients with poorly controlled type 2 diabetes and their family members.

### Trial objectives

• To examine the effects of a psychological, family-based intervention to improve biophysical, psychosocial and behavioural outcomes for patients with poorly controlled type 2 diabetes.

• To evaluate the experience of participating in the intervention.

## Methods/design

This study is a randomised controlled trial. In order to recruit a sufficiently large sample of patients with poorly controlled diabetes, participants are being recruited from diabetes specialist clinics, rather than from a primary care setting. In Ireland, the majority of patient's with type 2 diabetes in poor control of their illness are referred by their GP to a specialist clinic, and are mainly managed there. Thus, it would not have been possible to recruit the required number of participants in poor control of their diabetes from a primary care setting.

### Participants

There will be two groups of participants in the study; patients with poorly controlled type 2 diabetes and their family members. A record will be kept of all clinic attendees who do not wish to participate and their reasons for non-participation. Participants and non-participants will be compared across a number of variables (e.g. age, gender etc) to investigate any sub-group differences.

#### Inclusion and exclusion criteria

##### People with poorly controlled type 2 diabetes

People with type 2 diabetes are included in the trial if they are over 18 years of age, have fluency in English, have type 2 diabetes for more than one year, and at least two out of their last three HbA1c readings haven been 8.0% or over, in order to identify patients' with persistent poor control. (A HbA1C reading of 8% or over is a recognised value for poor metabolic control of diabetes [48].) Patients with a life-threatening physical illness (e.g. cancer, renal failure) will be excluded. Patients with a severe and enduring mental disorder (e.g. dementia, schizophrenia) as determined by the patients' clinician, will also be excluded. Patients not responsible for their own care, or those not residing in their home environment will be excluded (e.g. those in care homes, prison, in-patient hospital wards). Patients with hearing impairments will also be excluded. Patients who took part in the pilot study, and those who took part in a previous study conducted in the same diabetes clinic [33]will be excluded.

##### Family members of participants with type 2 diabetes

Participants with poorly controlled type 2 diabetes recruited to the study will be asked to nominate a family member to participate in the research with them. For the purposes of this study family members will be defined as any relative in regular contact with the person with diabetes, and who is most involved in supporting that person in the management of their illness. As most people with diabetes manage their illness themselves, the family member for this study is not a *carer*, but someone with whom the person with diabetes has a close relationship. This may include a spouse/partner, parent, grandparent, child, grandchild, siblings, or other family members. The inclusion criteria for a family member are that they must be over 18 years of age and have no medical history of type 1 or type 2 diabetes.

### Screening eligibility

Potential participants will be recruited from two diabetes specialist clinics at the AMNCH Hospital in Tallaght in Dublin. All type 2 patients over 18 years, with at least two of their last three HbA1c readings of 8.0% or greater (eligible participants), will be identified through the auditing facility of the "Diamond" computer database (n~ 3560 type 2). Prior to each clinic a list of eligible patients attending the clinic will be generated by the Diamond database, who will subsequently be asked to participate in the study (see Figure 3: Flowchart of RCT).

**Figure 3 F3:**
[figure not shown]
Flow Chart of RCT.

### Baseline assessment

During the twice-weekly out-patients clinics eligible patients will be approached by the researcher, given information about the study and invited to participate. On agreement, they will be asked provide their written informed consent, and to complete the baseline questionnaires with the researcher (this will take on average fifteen minutes). These questionnaires consist of demographic questions, the brief-illness perceptions questionnaire [49], the well-being 12 scale [50], the diabetes management self-efficacy scale [51], the diabetes family behaviour checklist [52]and the summary of diabetes self-care daily activities [53]). At this appointment time their HbA1c, blood pressure, and body-mass index will also be taken. The person with diabetes will also be given a questionnaire pack containing the family member measures, and asked to ensure their nominated family member completes the questionnaires and returns them by post to the researcher, prior to commencement of the intervention. The family member questionnaire include demographic questions, and adapted versions of the brief illness perceptions questionnaire [49]and the diabetes family behaviour checklist [52].

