### Outcome assessment

At six months post-intervention (approximately 24 weeks from the time of randomisation), control and intervention participants will be invited back to the diabetes clinic in the same staggered manner as they were recruited. At this time point, HbA1c, blood pressure, cholesterol and body-mass index will be taken again and recorded. The baseline questionnaires will also be re-administered. In addition, a record will be kept of participation rates throughout the intervention and reasons for non-participation where possible. Participants will again be given a questionnaire pack containing the family member measures, and asked to ensure that their nominated family member completes the questionnaires and returns them to the researcher by post.

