### Randomisation

After consent and baseline data have been collected from the first 40 patients, they will be randomized into intervention and control groups by using computer generated random number tables. The main investigators will not be involved in the randomisation procedure, which will be carried out by an independent expert. The use of block randomisation means that the intervention can be delivered in a staggered manner, with some participants beginning the intervention while further recruitment continues. When the next 40 patients are recruited, they will then be randomly allocated to intervention or control groups, and so on, until 122 patients are included in the trial. Due to the psychological nature of the intervention, it is not possible for the investigator delivering the intervention to be blind to participants' treatment allocation group.

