### Sample size and rate of recruitment

Taking HbA1c and Diabetes Well-being as primary outcomes, a total sample size of 76 and 86 respectively, were calculated. This was using 80% power to detect a significant *absolute *change of 0.9% in glycaemic control (this absolute change has been related to clinical outcomes in the UK prospective diabetes study, [3] and of 3 points in the Diabetes Well-being Scale-12. These calculations also allow for an anticipated "Hawthorn effect" relating to an improvement of 20% for those in the control group, by virtue of the fact that they are participating in the research. Taking the larger number of86 participants (43 inintervention and 43 in control group), a final total number of 122 participants (61 in each group) is needed to ensure at least a 70% final response rate is met. Previous research in the diabetes clinic [33] has shown that it is possible for one researcher to see approximately two to three eligible patients per clinic. Thus, it is estimated that it will take approximately 8–10 weeks to recruit the required 40 participants for the first block for randomisation.

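### At six months the self-reported primary outcome (Well-being) is re-administered in clinic, and nothing keeps the person doing so blind to allocation or separate from the interventionist

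*Protocol article*

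**What the plan says.** **Role of the outcome.** Under Sample size and rate of recruitment: "Taking HbA1c and Diabetes Well-being as primary outcomes, a total sample size of 76 and 86 respectively, were calculated". Well-being gives the larger number and so sets the trial's size.

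**Baseline.** Under Baseline assessment, the patient questionnaires include "the well-being 12 scale [50"], and patients are asked "to complete the baseline questionnaires with the researcher (this will take on average fifteen minutes"). This precedes allocation. Under Randomisation: "After consent and baseline data have been collected from the first 40 patients, they will be randomized into intervention and control groups".

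**Follow-up.** Under Outcome assessment, both arms return to the clinic at six months, where "The baseline questionnaires will also be re-administered". No person and no mode of completion is named. The family member's pack, by contrast, is completed away from the clinic and posted back at both time points.

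**Blinding and independence.** Randomisation contains the only blinding statement: "it is not possible for the investigator delivering the intervention to be blind to participants' treatment allocation group". It also contains a safeguard for allocation: "The main investigators will not be involved in the randomisation procedure, which will be carried out by an independent expert". Table 2 (Quality assurance) adds an independent expert to assess a sample of taped sessions. Neither safeguard covers the collection of outcomes.

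**Process questionnaire.** Table 2 also schedules open-ended questionnaires at follow-up data collection, for all participants in both arms, on their views of the intervention and of taking part.

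**The concern.** Well-being is a subjective score. By six months, intervention patients have had two home sessions and a telephone call using motivational interviewing techniques, while controls have had usual care. If the scale is again completed with a researcher who knows the allocation, two things can differ between arms: how patients wish to present themselves, and what the researcher expects or prompts. Either would shift the group difference without any true change in well-being.

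The other questionnaires that patients complete at that visit are exposed in the same way. HbA1c is a laboratory measure, and the family packs are posted, so both are little affected.

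The Quantitative analysis section sets the 5% level for primary outcomes and does not say that both must succeed. A claim could then rest on Well-being alone, which is the primary outcome open to this bias.

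An assessor who starts out blind may not stay so. Unless the open-ended questionnaire comes after the well-being scale, its answers can reveal the allocation at the same visit.

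**Working it through.** **1. Setting the sections side by side.**

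- Baseline assessment: completed with the researcher, before randomisation. No allocation exists yet, so this step cannot bias the comparison between arms.
- Outcome assessment: the same questionnaires, in clinic, after randomisation. No change of mode or person is stated, so the baseline mode is the only one on record.
- Randomisation: blinding is addressed for the interventionist only.
- Intervention: sessions are delivered by a health psychologist. Nothing says that this person is, or is not, the researcher.
- Sample size and rate of recruitment: clinic capacity is reckoned on one researcher. This makes overlap of roles possible but does not establish it.

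The exposure is therefore at six months, and no stated safeguard applies there.

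**2. The plan's own figure.** 86 / 0.70 = 122.9, which rounds up to 123 (124 with equal arms), against 122 stated. The figure reproduces to within two patients. The 86 itself cannot be rebuilt because no SD is given, so the SD must be back-calculated.

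**3. Implied SD.** Inputs from the document: 43 per arm, 80% power, 5% level, a 3-point difference, and a 20% allowance for improvement in controls. Two assumptions are added: the test is two-sided, and the comparison is of two means.

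SD = difference / [(1.960 + 0.842) × √(2/43)], where √(2/43) = 0.2157.

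- Full 3 points: 3 / (2.802 × 0.2157) = 4.97. The standard error is 3 / 2.802 = 1.071.
- If the 20% allowance cuts the difference to 0.8 × 3 = 2.4 points: 2.4 / (2.802 × 0.2157) = 3.97. The standard error is 2.4 / 2.802 = 0.857.

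**4. False-positive rate with no true effect and an assumed differential reporting shift b.**

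Rate = Φ(b/SE − 1.960) + Φ(−b/SE − 1.960)

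For b = 1 and SE = 1.071, b/SE = 0.934, so the rate is Φ(−1.026) + Φ(−2.894) = 15.4%.

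| Assumed shift between arms | Share of 3-point target | SD 4.97 | SD 3.97 |
|---|---|---|---|
| 0 | 0% | 5.0% | 5.0% |
| 0.5 points | 17% | 7.5% | 9.0% |
| 1.0 point | 33% | 15.4% | 21.5% |
| 1.5 points | 50% | 28.8% | 41.7% |

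The shifts are assumptions chosen to show the range. The document gives no estimate of the bias.

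**The case against.** The strongest reply is that this is silence in a condensed article. Who hands out forms at a clinic visit may be settled in the full protocol, and the trial flow chart is not shown. The blinding sentence is true as written and does not say that assessors know the allocation. This stands in part, and it is why the point is about what the text permits and not about what will happen. But the article does address blinding and independence, and it covers only the interventionist, the randomisation and the tape assessment. It also states a researcher-assisted mode for a primary outcome.

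A reader might infer several stronger things that the document does not support:

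- *That the baseline data are biased.* They are collected before allocation.
- *That follow-up is certainly face to face with the researcher.* This is a reasonable inference from re-administration in clinic, but it is not stated.
- *That the researcher is the person who treated the patient.* The article uses different terms for the roles and neither equates nor separates them.
- *That reactivity acts in the intervention arm only.* Controls attend the same visit, and the sample size section itself expects a 20% improvement in controls from taking part. Only the difference between arms matters. The allowance does not protect against that difference.
- *That every secondary questionnaire is affected.* The family packs are posted.

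Two practical objections also have weight. The Pilot study section reports that some participants found one self-efficacy measure hard to understand, so some help may be needed. And a change of mode between baseline and follow-up is undesirable in a repeated-measures analysis. Both argue for logging help and applying the change equally to the arms. Neither argues for leaving the procedure open.

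**Conclusion.** The point holds in limited form. As written, the plan allows a subjective primary outcome to be collected at six months by someone who knows the allocation, possibly the interventionist, and it states no safeguard. The result would be a difference in reporting between arms that could not be told apart from a treatment effect on Well-being or on the other patient-completed questionnaires.

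The size is unknown. The illustrative false-positive rates (about 7.5–9%, 15–22% and 29–42% for shifts of 0.5, 1.0 and 1.5 points) rest on an assumed bias, an SD back-calculated from the sample size, a two-sided test and 43 responders per arm. No single figure in that range should be read as this trial's error rate.

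It would also go too far to say that a positive trial could not be believed, because HbA1c is little exposed to this problem. The caution applies to a Well-being result standing alone. The change is worth making because it is cheap and leaves the sample size and analysis as they are.

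**What to change.** For the six-month visit, in both arms:

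1. Patients complete the well-being scale themselves, as the first study activity of the visit, before other study contact and before the open-ended process questionnaire. They seal it in an envelope.
2. The interventionist neither administers the scale nor is present.
3. Any help given is logged, with who gave it.
4. The protocol names the role that hands out and collects the form. The article does not say who takes the blood sample and other clinic measurements, so it should not be assumed that those staff are available for this.

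The same procedure is preferable for the rest of the patient pack.

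**Cost.** Procedure wording and envelopes, with no change to the sample size or the analysis. If one person turns out to hold both roles, someone else must hand out and collect the form. Some items will be missing. Patients already enrolled will have a different mode at follow-up than at baseline, equally in both arms.

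**Limit.** Patients know their allocation, so the bias is reduced and not removed. The report of the trial should say so.
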